## Abstract

**Background:**

Disease recurrence remains one of the biggest concerns in patients after resection of pancreatic ductal adenocarcinoma (PDAC). Despite (neo)adjuvant systemic therapy, most patients experience local and/or distant PDAC recurrence within 2 years. High-level evidence regarding the benefits of recurrence-focused surveillance after PDAC resection is missing, and the impact of early detection and treatment of recurrence on survival and quality of life is unknown. In most European countries, recurrence-focused follow-up after surgery for PDAC is currently lacking. Consequently, guidelines regarding postoperative surveillance are based on expert opinion and other low-level evidence. The recent emergence of more potent local and systemic treatment options for PDAC recurrence has increased interest in early diagnosis. To determine whether early detection and treatment of recurrence can lead to improved survival and quality of life, we designed an international randomized trial.

**Methods:**

This randomized controlled trial is nested within an existing prospective cohort in pancreatic cancer centers in the Netherlands (Dutch Pancreatic Cancer Project; PACAP) and the United Kingdom (UK) (Pancreas Cancer: Observations of Practice and survival; PACOPS) according to the “Trials within Cohorts” (TwiCs) design. All PACAP/PACOPS participants with a macroscopically radical resection (R0-R1) of histologically confirmed PDAC, who provided informed consent for TwiCs and participation in quality of life questionnaires, are included. Participants randomized to the intervention arm are offered recurrence-focused surveillance, existing of clinical evaluation, serum cancer antigen (CA) 19–9 testing, and contrast-enhanced computed tomography (CT) of chest and abdomen every three months during the first 2 years after surgery. Participants in the control arm of the study will undergo non-standardized clinical follow-up, generally consisting of clinical follow-up with imaging and serum tumor marker testing only in case of onset of symptoms, according to local practice in the participating hospital. The primary endpoint is overall survival. Secondary endpoints include quality of life, patterns of recurrence, compliance to and costs of recurrence-focused follow-up, and the impact on recurrence-focused treatment.

**Discussion:**

The RADAR-PANC trial will be the first randomized controlled trial to generate high level evidence for the current clinical equipoise regarding the value of recurrence-focused postoperative surveillance with serial tumor marker testing and routine imaging in patients after PDAC resection. The Trials within Cohort design allows us to study the acceptability of recurrence-focused surveillance among cohort participants and increases the generalizability of findings to the general population. While it is strongly encouraged to offer all trial participants treatment at time of recurrence diagnosis, type and timing of treatment will be determined through shared decision-making. This might reduce the potential survival benefits of recurrence-focused surveillance, although insights into the impact on patients’ quality of life will be obtained.

**Trial registration:**

Clinicaltrials.gov, NCT04875325. Registered on May 6, 2021.

## Administrative information

Note: the numbers in curly brackets in this protocol refer to SPIRIT checklist item numbers. The order of the items has been modified to group similar items (see http://www.equator-network.org/reporting-guidelines/spirit-2013-statement-defining-standard-protocol-items-for-clinical-trials/).

**Table Taba:** 

Title {1}	Recurrent diseAse Detection After Resection of PANCreatic ductal adenocarcinoma using a recurrence-focused surveillance strategy (RADAR-PANC) – protocol of an international randomized controlled trial according to the Trials within Cohorts design
Trial registration {2a and 2b}.	Clinicaltrials.gov registration, NCT04875325. Registered on 6 May 2021, https://clinicaltrials.gov/study/NCT04875325?term=NCT04875325&rank=1
Protocol version {3}	Version 4.0, October 24, 2023
Funding {4}	Funded by Deltaplan Alvleesklierkanker

## Introduction

### Background and rationale {6a}

#### Background

Pancreatic ductal adenocarcinoma (PDAC) is the fourth leading cause of cancer related mortality in Europe for both men and women and is expected to rise to the second position by 2030 [1, 2]. For patients with localized disease, radical resection combined with systemic therapy offers the best chance of long-term survival and can be curative in some cases [3, 4]. However, almost all patients experience local and/or distant disease recurrence at some point during follow-up [5–8]. Therefore, even after PDAC resection, median overall survival remains less than 2 years, with only 4% of patients surviving over 10 years [3, 9].

Current research is mainly focused on management of primary or metastatic PDAC, with most trials evaluating treatment strategies for primary resectable or locally advanced PDAC. Studies regarding the efficacy and optimal timing of treatment for recurrence are scarce. As a result, prospective evidence on survival benefits following early detection and treatment of recurrence is lacking and the effect on quality of life (QoL) remains unknown. This has led to conflicting recommendations on follow-up after resection of PDAC, and current PDAC guidelines regarding postoperative surveillance are based on expert opinion and other low-level evidence (Table 1) [10–16].

**Table 1 Tab1:** Current guidelines and follow-up

Medical society	Recommendation	Level of evidence
National Comprehensive Cancer Network (NCCN—2018) [11]	Clinical evaluation every 3–6 months for 2 years, then annually	Uniform expert opinion (2A)
	CA 19–9, CT scan every 3–6 months for 2 years, then annually	Non-uniform expert opinion (2B)
European Society for Medical Oncology (ESMO—2015) [12]	No evidence that regular follow-up after therapy with curative intent has any impact on outcome	No evidence (4D)
	Follow-up should concentrate on symptoms, nutrition, and psycho-social support	No evidence (4D)
Japan Pancreas Society (2013) [13]	Measurement of tumor markers and a dynamic CT scan every 3 to 6 months for 2 years postoperatively and every 6 to 12 months subsequently, at least for 5 years postoperatively	Low (C)
American Society of Clinical Oncology (ASCO—2017) [14]	History and physical evaluation every 3–6 months after completion of therapy. Additional serum CA 19–9 if elevated pre-operatively	Uniform expert opinion (2A)
	Benefit of imaging is unclear; it seems to result in greater detection of asymptomatic recurrence	
	Primary focus on treatment-related toxicity, survivorship issues, and recurrence monitoring	
National Dutch Guideline Pancreatic carcinoma (NVvH—2019) [15]	Clinical follow-up. In case of symptoms of disease recurrence, additional diagnostic testing can be used	Uniform expert opinion (2A)
	Consider routine diagnostic follow-up in an investigative context only	Low (C)
International Association of Pancreatology/European Pancreatic Club (IAP/EPC—2016) [16]	No recommendation	Not applicable

Recent introduction of more potent systemic therapies, such as fluorouracil, leucovorin, irinotecan and oxaliplatin (FOLFIRINOX) and gemcitabine/nab-paclitaxel combination therapy, and local ablative therapies, such as stereotactic body radiation therapy (SBRT), has opened the field for treatment of PDAC recurrence [4, 17]. Despite a lack of evidence, this has resulted in an increased interest in recurrence-focused postoperative surveillance with routine imaging and serial serum tumor marker testing, with the ultimate goal to detect PDAC recurrence at an early asymptomatic stage [18]. This hypothetically leads to the identification of patients with a good performance status who are most likely to tolerate (experimental) treatment [19]. However, it remains unclear whether all patients with asymptomatic PDAC recurrence can be treated and whether early initiation of recurrence-focused treatment results in improved oncological outcomes. Moreover, early initiation of recurrence treatment in asymptomatic patients might induce treatment-related toxicity, which could worsen quality of life. Recurrence-focused surveillance could also increase fear of cancer recurrence, which negatively impacts quality of life, as might detection of recurrence in an asymptomatic stage [20, 21]. Consequently, in most European countries including the Netherlands and the United Kingdom (UK), ethical concerns towards a recurrence-focused follow-up are raised and guidelines do not recommend a recurrence-focused follow-up strategy [11, 14].

#### Rationale

The RADAR-PANC trial is designed to investigate whether a recurrence-focused surveillance strategy with serial tumor marker testing and routine imaging improves overall survival in patients after radical resection for PDAC in the Netherlands and the UK, compared to current non-standardized follow-up. Furthermore, the consequences of a recurrence-focused surveillance strategy on quality of life and additional (experimental) treatment will be assessed.

### Objectives {7}

The main objective of this study is to investigate whether recurrence-focused surveillance with three-monthly serum tumor marker testing and computed tomography (CT) imaging improves survival of patients with primary resected PDAC.

We hypothesize that patients who receive recurrence-focused surveillance will be diagnosed with PDAC recurrence at an earlier stage (i.e., localized disease and a good performance status). This hypothetically increases the number of patients that could tolerate (experimental) treatment for recurrence, with subsequent potential survival benefits. The goal of recurrence-focused surveillance will therefore be to improve overall survival.

The secondary objectives of this study are as follows:To evaluate the impact of recurrence-focused surveillance on quality of lifeTo evaluate compliance to a recurrence-focused surveillance strategyTo evaluate the impact of recurrence-focused follow-up on worry of cancer recurrenceTo evaluate disease-free survivalTo assess clinical and radiological patterns of PDAC recurrenceTo assess the role of serum tumor marker testing in detecting recurrent PDACTo assess eligibility for recurrence-focused (experimental) systemic and/or local treatmentTo evaluate reasons to refrain from treatment for recurrence (i.e., eligibility, deteriorated condition, patient’s wish, doctors’ advice, etc.)To assess patients’ tolerance for treatment for recurrenceTo assess prognostic factors for asymptomatic PDAC recurrenceTo calculate the cost-efficacy of a recurrence-focused follow-up

### Trial design {8}

The RADAR-PANC trial is an international randomized controlled trial nested within two large nationwide prospective cohorts (the Dutch Pancreatic Cancer Project; PACAP, and the UK Pancreas Cancer: Observations of Practice and survival; PACOPS) and follows the “Trials within Cohorts” (TwiCs) design [22]. With this design, a large observational cohort of patients is recruited and used as a multiple trials facility, and “patient-centered” information and consent are provided an obtained. For each randomized controlled trial, eligible patients are identified within the cohort and randomized [23]. The TwiCs design improves trial participation by avoiding non-participation on the basis of patients’ or doctors’ preference for the intervention.

In 2013, PACAP was initiated by the Dutch Pancreatic Cancer Group (DPCG) [24]. The UK PACOPS project was established in 2023 and follows the same setup as PACAP. Within these projects, patients with PDAC are asked to participate in the PACAP/PACOPS cohort at diagnosis. First, patients are asked general informed consent for collection of specific data on demographics and clinical, laboratory and radiological findings before, during, and after treatment and follow-up. Second, patients are asked to provide informed consent for participation in quality of life questionnaires to assess Patient Reported Outcome Measurements (PROMs). Third, patients are asked to provide informed consent for being randomized in future studies according to the TwiCs design. At the time informed consent is signed, neither the patient nor the researcher knows for which studies this patient is or might become eligible. This is called a “broad” consent, since patients do not know for which specific research questions their data may be used in the future [23]. Participants are only informed in case they can actually receive the intervention, i.e., when randomized to the intervention arm. If they then choose to undergo the intervention, they provide additional informed consent (two-staged informed consent) [25]. Patients randomized to the control arm are not further notified and followed in the context of the prospective cohort study, according to the current, non-standardized best practice. This approach is thought to reduce disappointment bias and cross-over of patients randomized to the control arm of the study. Importantly, at cohort enrolment, patients are adequately informed that at some point during their treatment or follow-up, they may be serving as control without being explicitly notified, which was demonstrated to be positively or neutrally received among patients [26].

## Methods: participants, interventions, and outcomes

### Study setting {9}

International, multicenter randomized controlled trial (NCT04875325).

### Eligibility criteria {10}

Patients are eligible for randomization if they meet all of the following criteria:Participation in the PACAP or PACOPS cohortMacroscopic radical resection (R0-R1) of histologically confirmed PDACAge ≥ 18 yearsWritten informed consent for being randomized in future studies (TwiCs) and participation in quality of life questionnaires (PROMs)

A potential study participant who meets any of the following criteria is excluded:Contraindications for contrast-enhanced CT imaging, following the protocol of the department of radiology in each participating hospitalMentally or physically incapable of giving consentParticipation in other studies with a study-specific follow-up comprising imaging and/or serum tumor marker testing

### Who will take informed consent? {26a}

The inclusion and randomization process of the RADAR-PANC trial is schematically shown in Fig. 1. Potentially eligible subjects are identified by the (local) investigator or an authorized delegate, by checking pathology reports of patients with known or suspected PDAC after intended radical resection. The (local) investigator or an authorized delegate will confirm that a potentially eligible patient is included in the PACAP or PACOPS cohort and signed informed consent for being randomized in future studies according to the TwiCs design and participation in quality of life questionnaires. If not, the patient will continue standard of care and will not be randomized for this trial. If the patient meets all the eligibility criteria for the RADAR-PANC trial, the participant is randomized for postoperative surveillance strategy with a 1:1 allocation ratio. Participants are either randomized for follow-up according to the current, non-standardized practice (control), or recurrence-focused surveillance according to the trial protocol (intervention). If the patient is randomized to the control arm, no additional action is taken: patients will receive current standard of care and are not explicitly informed about being randomized to the control arm of the trial according to the TwiCs design. Patients randomized to the intervention arm of the trial will be approached by a researcher and will be offered the experimental intervention within the first 3 to 4 months post-surgery. These patients are informed that they are free to decide whether they want to accept or deny the intervention. Oral and written information is provided and the treating physician is informed. If the patient chooses to participate, the additional informed consent form is signed prior to the start of the intervention.

**Fig. 1 Fig1:**
[figure not shown]
Schematic inclusion and randomization process of the RADAR-PANC trial. PDAC pancreatic ductal adenocarcinoma, TwiCs Trials within Cohorts, PROMs patient-reported outcome measures, CT computed tomography, CA carbohydrate antigen, BSC best supportive care

### Additional consent provisions for collection and use of participant data and biological specimens {26b}

All participants in the RADAR-PANC trial are already participating in PACAP or PACOPS and have already provided broad informed consent for the use of their medical data prior to inclusion in the current trial. Consequently, no additional consent for further studies is needed for collection and use of participant data.

### Interventions

#### Explanation for the choice of comparators {6b}

Participants in the control arm of the RADAR-PANC trial will receive non-standardized clinical follow-up, according to local practice in the participating hospital. As the most recent version of the national Dutch guideline for PDAC care currently does not recommend a recurrence-focused follow-up frequency, methodology, or focus, follow-up after PDAC resection is based on shared decision-making, at the discretion of the treating clinician and the patients’ wish [15].

### Intervention description {11a}

The intervention exists of a recurrence-focused follow-up approach with routine imaging and serial serum tumor marker testing. The follow-up scheme of the RADAR-PANC trial is based on current surveillance guidelines after resection for PDAC as recommended by the National Comprehensive Cancer Network (NCCN) [11]. This intense follow-up scheme was chosen to increase the chance of early diagnosis of disease recurrence. For the first 2 years after surgery, clinical evaluation, serum carbohydrate antigen 19–9 (CA 19–9) testing, and contrast-enhanced CT imaging of chest and abdomen is performed every 3 months.

Follow-up of patients and related procedures (i.e., blood draws, CT scans) in this study can be performed at the participating hospital, referring hospital, or central coordinating hospital. Study-related follow-up is performed at 3, 6, 9, 12, 15, 18, 21, and 24 months after surgery. For the first follow-up evaluation, patients need to be randomized within the first 3 to 4 months post-surgery. Follow-up appointments are made by the trial coordinator in consultation with the treating clinician. If possible, outpatient clinic visits are combined with CT scan appointments; blood samples are obtained simultaneously.

#### Blood samples

At 3 months postoperatively and every subsequent 3 months during the first 2 years of follow-up, blood samples are obtained from study participants to assess CA 19–9 values. In addition, serum bilirubin is also determined to assess adjusted CA 19–9 levels.

#### CT imaging

During the first 2 years of follow-up, a CT of chest and abdomen with intravenous contrast (late arterial phase of the upper abdomen and portal venous phase covering the entire abdomen) is performed at 3 months postoperatively and every subsequent 3 months.

#### Quality of life assessment

All study participants, either randomized for the intervention or control arm of the RADAR-PANC trial, will receive quality of life questionnaires at each follow-up appointment, in the context of the PACAP and PACOPS cohort studies. The following questionnaires are used: non-disease specific health-related quality of life (HRQL) (EQ-5D-5L), cancer-specific HRQL (EORTC QLQ-C30), tumor-specific HRQL (EORTC QLQ-PAN26), hospital anxiety and depression scale (HADS), and worry of progression of cancer scale (WOPS; modified Dutch seven-item version of the six-item English cancer worry scale (CWS)) [27–31].

#### Recurrence diagnosis

If disease recurrence (local and/or distant) is suspected on the basis of a follow-up CT scan, with or without elevated tumor markers, pathological confirmation is strongly advised. If the results remain inconclusive or pathology cannot be obtained, additional imaging (magnetic resonance imaging (MRI) and/or positron emission tomography CT (PET-CT)) may be considered. Consensus on the presence of a recurrence should be obtained in a multidisciplinary meeting (e.g., based on imaging, elevated CA 19–9, and clinical evaluation).

If disease recurrence is diagnosed, best supportive care (BSC) or systemic and/or local therapy is offered at the discretion of the treating clinician in both trial arms, which is the current standard practice, and trial-related follow-up will end. It is encouraged to offer treatment to all patients in whom there are no contraindications based on clinical condition (performance status), comorbidity, or specific exclusion criteria for systemic and/or local therapy. Patients can be offered to participate in intervention trials on management of pancreatic cancer recurrence. In the Netherlands, within the DPCG, two intervention studies for the treatment of PDAC recurrence have been simultaneously initiated: the ARCADE trial (NCT04881487), investigating the efficacy of stereotactic body radiation therapy on survival after recurrence and quality of life in patients with isolated local PDAC recurrence, and the TIMEPAN trial (NCT04897854) studying the optimal timing of start of systemic treatment for asymptomatic metastasized PDAC.

### Criteria for discontinuing or modifying allocated interventions {11b}

Participants may withdraw from participation in the RADAR-PANC study at any time and for any reason without consequence. The principal investigator may withdraw a patient from the study for one or more of the following reasons: the patient is not following the research staff's instructions of the protocol, continued participation could be harmful to the patient, and other administrative reasons or unforeseen circumstances.

If participants become too ill to attend their follow-up visits, the study team will continue to send quality of life questionnaires and obtain data through the patients’ general practitioner.

### Strategies to improve adherence to interventions {11c}

For full adherence to the study protocol, the trial coordinator is responsible for arranging all follow-up appointments and diagnostic tests for patients, in consultation with the treating physician at the participating or referring center. Diagnostic testing can be performed either at the local participating center as well as at the referring center or the central coordinating center, as desired by the patient. The trial coordinator will monitor whether follow-up measurements have been completed, including diagnostic tests as well as quality of life questionnaires.

### Relevant concomitant care permitted or prohibited during the trial {11d}

Concomitant care and interventions will not be prohibited during the trial.

### Provisions for post-trial care {30}

Individual patients will remain enrolled in the RADAR-PANC trial for a maximum of 2 years or until patient withdrawal. Follow-up of patients that have completed the 2-year follow-up will be continued for survival information until death. Patients who are withdrawn from the study will be followed-up by a medical specialist or general practitioner for survival information until death. After the study period has ended for an individual patient, continuation of either recurrence-focused or non-standardized follow-up and diagnostic testing is based on shared decision-making between patients and their treating physicians.

### Outcomes {12}

The primary outcome is overall survival, defined as the time from the date of PDAC resection until the date of either death from any cause or last follow-up.

Secondary outcomes are the following:Patient-reported quality of life and worry of cancer recurrence, as measured by PROMs questionnaires within the PACAP-PROMs and PACOPS project: general EORTC QLQ-C30 and EQ5D-5L, pancreas-specific EORTC QLQ-PAN26, HADS, and WOPS.Compliance to recurrence-focused surveillance, measured as the percentage of patients that either accepts or refuses participation in the intervention-arm, i.e., is willing to undergo recurrence-focused follow-up.Disease-free survival, defined as the interval between the date of PDAC resection and the date of first radiological signs of recurrence, or last follow-up if recurrence is not observed. Preferably, recurrence is proven by a biopsy showing pathological confirmation of recurrent PDAC. However, recurrence can be clinically confirmed with growth of a suspicious lesion on consecutive CT scans and elevation of CA 19–9 (> 37 U/ml) and/or activity on PET-CT following consensus in a multidisciplinary meeting.Clinical and radiological patterns of disease recurrence:◦ Asymptomatic recurrence is defined as PDAC recurrence detected by CT imaging during follow-up, in the absence of suspected symptoms. If PDAC recurrence is discovered due to a significant patient-initiated complaint that is new or has been increased in severity or frequency, disease recurrence is defined as symptomatic.◦ Localization of recurrence is categorized using five categories: (1) isolated locoregional recurrence: recurrence in the pancreatic remnant, locoregional lymph nodes, or surgical bed, such as soft tissue along the celiac or superior mesenteric artery, aorta, or around the pancreatojejunostomy site; (2) isolated distant recurrence: recurrence restricted to a single organ or site; (3) local + distant recurrence: simultaneous occurrence of both isolated locoregional recurrence and isolated distant recurrence; (4) multiple recurrence: recurrence at multiple distant sites; and (5) peritoneal carcinomatosis.The yield of CT surveillance and role of serum tumor marker testing in detecting PDAC recurrence, by calculating diagnostic accuracy values, i.e., sensitivity, specificity, positive predictive values, and negative predictive values.Eligibility for additional (experimental) treatment at time of recurrence diagnosis, based on the Eastern Cooperative Oncology Group (ECOG) or Karnofsky performance state, or inclusion criteria for study-related treatment of recurrence.Reasons to refrain from treatment for recurrence (i.e., non-eligibility, deteriorated condition, patient’s wish, doctors’ advice, progression during treatment, etc.).Patients’ tolerance to treatment for recurrence, measured by the reasons to stop treatment for recurrence (i.e., per protocol, deteriorated condition, patient’s wish, doctors’ advice, progression during treatment etc.).Morbidity associated with recurrence-focused treatment.Overall costs of recurrence-focused surveillance vs. costs as incurred with current non-standardized follow-up. Cost-effectiveness is examined through the EQ5D questionnaire and calculated using a Markov model.

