## Abbreviations

ASCO: American Society of Clinical Oncology
Asymptomatic PDAC recurrence: PDAC recurrence detected by CT imaging during follow-up, in the absence of suspected symptoms
BMI: Body mass index
BSC: Best supportive care
CA 19-9: Carbohydrate antigen 19–9
CCI: Charlson comorbidity index
CI: Confidence interval
Clinically confirmed recurrence: 2/3 Of the following criteria: -Growth of a suspicious lesion on consecutive CT scans, -Elevation of CA 19–9 (> 37 U/ml), -Abnormal activity on PET-CT
CT: Computed tomography
CTCAE: Common Terminology Criteria for Adverse Events
CWS: Cancer worry scale
Disease-free survival: The interval between the date of surgery and either the date of first radiological signs of recurrence, or last follow-up if recurrence is not observed
DPCG: Dutch Pancreatic Cancer Group
DSMB: Data Safety Monitoring Board
EORTC QLQ-C30: Cancer-specific health-related quality of life
EQ-5D-5L: Non-disease specific health-related quality of life
ECOG: Eastern Cooperative Oncology Group
ESMO: European Society for Medical Oncology
FOLFIRINOX: Fluorouracil, leucovorin, irinotecan, and oxaliplatin
HADS: Hospital anxiety and depression scale
HQRL: Health-related quality of life
HR: Hazard ratio
IAP/EPC: International Association of Pancreatology/European Pancreatic Club
IQR: Interquartile range
MD: Mean differences
MID: Minimally important difference
MREC/METC: Medical research ethics committee (MREC); in Dutch: medisch ethische toetsing commissie (METC)
MRI: Magnetic resonance imaging
NCCN: National Comprehensive Cancer Network
NFU: The Netherlands Federation of University Medical Centers; in Dutch: Nederlandse Federatie van Universitaire Medische Centra
NVvH: In Dutch: De Nederlandse Vereniging voor Heelkunde
Overall survival: The time from the date of resection of PDAC until either the date of death from any cause or date of last follow-up
PACAP: Dutch Pancreatic Cancer Project
PACOPS: Pancreas Cancer: Observations of Practice and Survival
PDAC: Pancreatic ductal adenocarcinoma
PDAC recurrence: Pathologically or clinically proven recurrence of PDAC
PET-CT: Positron emission tomography—computed tomography
PROMs: Patient reported outcome measurements
QoL: Quality of life
Radical resection: Macroscopically radical resection, i.e., R0-R1 resection
RAKU/RACU: Regional Academic Cancer center Utrecht
RH: Relative hazard
UK: United Kingdom
SBRT: Stereotactic Body Radiation Therapy
SD: Standard deviation

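### Disease-free survival omits death as an event, so under unequal imaging its planned between-arm comparison is biased in favour of the control arm (secondary endpoint; should fix)

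*Protocol article*

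**What the plan says.** Outcomes {12} measures DFS from resection to "the date of first radiological signs of recurrence, or last follow-up if recurrence is not observed". The Abbreviations entry gives the same end point: "either the date of first radiological signs of recurrence, or last follow-up if recurrence is not observed". Death appears in neither. For overall survival, by contrast, Outcomes {12} names it explicitly: "the date of either death from any cause or last follow-up".

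The arms are imaged differently by design. In the intervention arm, for the first 2 years, "contrast-enhanced CT imaging of chest and abdomen is performed every 3 months" (Intervention description {11a}). Control follow-up, in the abstract's Methods, generally has "imaging and serum tumor marker testing only in case of onset of symptoms".

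Statistical methods {20a} compares DFS between groups by Kaplan–Meier curves and a log-rank test, with a Cox model when appropriate.

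Clinically confirmed recurrence is defined twice. Outcomes {12} asks for "growth of a suspicious lesion on consecutive CT scans and elevation of CA 19–9 (> 37 U/ml) and/or activity on PET-CT", after multidisciplinary consensus. The Abbreviations list asks for "2/3 Of the following criteria: -Growth of a suspicious lesion on consecutive CT scans", the other two being raised CA 19-9 and abnormal PET-CT activity.

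**The concern.** An endpoint called disease-free survival normally fails at recurrence or death. Here the only dated failure is a radiological one. A patient who dies of an unimaged recurrence contributes no event and counts as disease-free up to the last contact. The Introduction says almost all patients recur, so such deaths are mostly disease-related and the censoring is informative. Kaplan–Meier and log-rank methods assume that it is not.

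In most trials this would blur both arms alike. Here the randomised intervention is itself the imaging, so whether a recurrence is seen before death depends on allocation. More missed events are to be expected among controls, and surveillance could appear to shorten DFS when disease is identical in the two arms. The Discussion recognises the mechanism: it sets post-recurrence survival aside as main endpoint because the recurrence date depends strongly on the surveillance strategy. It applies no such caution to DFS, which uses the same date.

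The two definitions of clinical confirmation add a smaller problem, since one patient can be an event under one and not under the other.

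**Working it through.** **What the rule does.** The protocol gives no design figure for DFS, so there is none to reproduce. Applying the definition to each type of patient:

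| Patient | DFS under the written rule |
|---|---|
| Recurrence seen on imaging | Event at first radiological signs |
| Alive, no recurrence observed | Censored at last follow-up |
| Dies, no recurrence observed | Censored at last follow-up (death not named) |
| Recurrence established without imaging | Date not defined |

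**Inputs from the protocol.** Sample size {14}: 20% of the intervention arm expected to refuse, and 5% of controls receiving routine imaging. Statistical methods {20c}: refusers are analysed in the intervention arm.

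**Assumptions (not in the protocol).** Disease is identical in both arms, so the true DFS hazard ratio (HR) is 1.00. Time to recurrence is Weibull (shape 1.2, scale 14 months). Survival after recurrence is exponential with median 8 months, giving a median overall survival of about 21 months. Administrative censoring is uniform over 30–58 months. A share of patients has no recurrence documented before death: *c* under control-type follow-up and *s* under surveillance.

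**Step 1: shares by randomised arm.**

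Intervention = 0.80·*s* + 0.20·*c*; control = 0.95·*c* + 0.05·*s*.

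- *c* = 10%, *s* = 3%: intervention 2.4 + 2.0 = 4.4%; control 9.5 + 0.15 = 9.65%
- *c* = 20%, *s* = 5%: intervention 4.0 + 4.0 = 8.0%; control 19.0 + 0.25 = 19.25%
- *c* = 30%, *s* = 5%: intervention 4.0 + 6.0 = 10.0%; control 28.5 + 0.25 = 28.75%

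**Step 2: simulated Cox HR, intervention versus control (true value 1.00).**

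| *c* / *s* | As written, no refusal or contamination | As written, after 20% refusal and 5% control imaging | Same, death counted as event |
|---|---|---|---|
| 10% / 3% | 1.15 | 1.10 | 1.05 |
| 20% / 5% | 1.32 | 1.24 | 1.11 |
| 30% / 5% | 1.62 | 1.44 | 1.19 |

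The last two columns are the relevant ones for an intention-to-treat comparison.

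**Step 3: how much does counting death remove?** On the log scale, the part left is ln 1.05 / ln 1.10 = 0.51, ln 1.11 / ln 1.24 = 0.49 and ln 1.19 / ln 1.44 = 0.48. About half of the bias remains.

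**Step 4: timing of detection.** The model above ignores detection delay. A second model assumed median time to detectable recurrence 10 months, median survival after it 8 months, 3-monthly CT to month 24, full uptake, and a share *q* of recurrences never scanned outside scheduled CT.

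| Mean delay to symptom-driven scan | *q* | HR as written | HR, death as event |
|---|---|---|---|
| 0 | 0 | 1.00 | 1.00 |
| 0 | 10% / 20% / 30% | 1.15 / 1.31 / 1.52 | 1.08 / 1.13 / 1.19 |
| 3 months | 0 | 1.23 | 1.08 |
| 3 months | 10% / 20% / 30% | 1.44 / 1.65 / 1.93 | 1.15 / 1.21 / 1.29 |

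These values assume no refusal, so they overstate the intention-to-treat effect. Their use is to show that a bias remains after the fix when detection is delayed, even if no recurrence goes permanently unscanned (3-month delay, *q* = 0: 1.08).

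**Step 5: the two confirmation rules.** Without biopsy, raised CA 19-9 plus PET-CT activity but no CT growth meets the Abbreviations rule and fails the Outcomes {12} rule, which has growth as a fixed element. The other pairs (growth with either of the two) satisfy both.

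**The case against.** **Importance.** DFS is one of many secondary outcomes. Overall survival is primary and counts death, and the Discussion ranks quality of life as the most important secondary endpoint. No sample size depends on DFS. The error disfavours surveillance, so it cannot manufacture a DFS benefit. This stands and limits the severity.

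**Reach.** A reader might infer that control patients who die never count as DFS events. The documents do not support that: a control who deteriorates is the patient for whom symptom-driven imaging is meant, and about 5% are expected to have routine imaging. Only those who die unscanned, or are scanned late, are affected. Nor does the protocol state that deaths are censored. That follows from its last-follow-up clause together with the absence of death in both definitions. For a recurrence established clinically without a scan, the text leaves the date undefined rather than prescribing censoring.

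**Size.** No document gives the share dying without documented recurrence. A reader might take an HR of about 1.6 as the expected bias. That figure ignores the protocol's own 20% refusal: in the 30% / 5% scenario refusers alone would contribute 20% × 30% = 6% missed in the intervention arm, already more than 5%. With shares as small as 5% and 2%, the diluted HR is only about 1.05.

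**Remedy.** Counting death does not equalise detection. Nor does a cumulative-incidence analysis with death as a competing event: an unscanned control who recurs and dies becomes a competing death, so control recurrence is still undercounted. Both points stand.

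**Confirmation rules.** The divergence is confined to one combination of findings, and the wording in Outcomes {12} is loosely punctuated. It is real but minor.

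**Conclusion.** The DFS definition is wrong as written. It omits death in both places, and following it censors deaths without observed recurrence informatively and unequally by arm. The direction, falsely longer DFS in controls, follows from the imaging schedules so long as more patients die without a documented recurrence under symptom-driven follow-up than under surveillance. The size is assumption-based: HR about 1.10 to 1.44 against a true 1.00 for the shares shown, after the protocol's refusal and contamination rates. With death as an event this falls to about 1.05 to 1.19, and more would remain with delayed detection.

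Severity is should-fix. The primary overall survival result is untouched, and nothing here supports reading the point as a threat to it.

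**What to change.** 1. In Outcomes {12} and the Abbreviations, define DFS as time from resection to the first of recurrence or death from any cause, with censoring at last follow-up only for patients alive without recurrence.
2. State that a recurrence established without imaging is dated by the multidisciplinary diagnosis.
3. Reconcile the two definitions of clinically confirmed recurrence and use one in both places.
4. State in the DFS analysis that unequal imaging schedules leave residual detection-time bias, as the Discussion already accepts for the recurrence date, and that the between-arm comparison is therefore descriptive. If recurrence alone is also reported, call it time to recurrence and attach the same caveat; a competing-risk analysis does not remove it.

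Cost: a protocol or analysis-plan amendment before the final analysis. Survival follow-up until death is already provided for under Provisions for post-trial care {30}, so no new patients, visits or scans are needed. The real concession is a weaker claim for the DFS comparison, because rewording alone cannot remove the residual bias.
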